### Sample Size

#### Phase 1

Bhutta et al [8] reported that the rates of clinical infections among children with complicated SAM vary from 15% to 68%. Considering 50% prevalence of lower respiratory tract infection among children with uncomplicated SAM, 95% CIs, 10% relative precision, 1.5% design effect, 10% nonresponse rate, and 5% type I error, we will require 606 participants aged 6-59 months with uncomplicated SAM.

#### Phase 2

A purposive sampling strategy will be followed to select participants. Primary caregivers of children with uncomplicated SAM will be identified based on their volunteerism and participation. Yadadri Bhuvanagiri District comprises four project areas (Bhongiri, Aler, Mothkur, and Ramanapeta), each consisting of multiple sectors and each sector covering 25 *Anganwadi*s [38]. FGDs are planned at the project level to ensure adequate representation across geographic areas and variations in the distribution of children with uncomplicated SAM. Initially, two FGDs are planned per project area; however, considering the larger geographic coverage and higher caseload in two project areas, an additional FGDs will be conducted in each of these areas based on data flow. In total, 10-12 FGDs will be conducted to capture diversity in experiences and practices across the district. Each FGD will include 8-10 participants.

As the aim is also to explore barriers and facilitators related to the management of children with uncomplicated SAM, IDIs are planned to include service providers across different levels of the health system. This approach reflects the continuum of care, as a child with uncomplicated SAM encounters multiple providers at different points within the health system. Therefore, two IDIs will be conducted in each health care worker group: Accredited Social Health Activist (ASHA), *Anganwadi* teacher (center), ANM (subcenter), MO (PHC), and pediatrician (district hospital and tertiary care center).

The data saturation principle will guide the final number of FGDs and IDIs to be conducted. Saturation will be considered achieved when no new themes, patterns, or insights emerge from successive FGDs or IDIs and when there is redundancy in the information obtained. Data collection and analysis will be undertaken simultaneously to monitor saturation, and additional FGDs or IDIs will be conducted, if required.

#### Phase 3

Rao et al [34] reported the WHZ mean (SD) as –1.29 (0.84) in the amoxicillin group and –1.45 (0.93) in the control group at the end of 2 weeks of intervention. Considering these values, with 95% CI and 80% power, we will require 480 participants in each group. Considering logistic issues, feasibility, and long follow-up, we will recruit 250 children aged 6-59 months with uncomplicated SAM per group.

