A list of children with uncomplicated SAM will be obtained from the NHTS website. The children will be visited at their homes to confirm their nutritional category. At enrollment, each child will be assigned a unique identification number based on the number in the list. After baseline assessment, children will be randomized using stratified randomization to one of three groups: amoxicillin (5 days, twice a day, 15 mg/kg based on weight band + standard nutritional care), azithromycin (single dose, 20 mg/kg + standard nutritional care), or control (no antibiotics + standard nutritional care). Children with subclinical infection will be randomized to either the amoxicillin or the azithromycin group in a 1:1 allocation ratio. Children without any subclinical infection will be randomized to the amoxicillin, azithromycin, or control group in a 1:1:2 randomization sequence to balance the stratified randomization based on subclinical infection status. The remaining children who will be assessed clinically for uncomplicated SAM, who pass the appetite test, and who are found eligible will be assigned to one of the three groups in a 1:1:1 randomization sequence; these children will be recruited after completion of the phase 1 enrollment. Around 150-200 participants are expected to be recruited after phase 1 enrollment to fulfill the sample size requirement for phase 3.

Three separate randomization sequences of unequal block sizes will be generated. A non–peer-reviewed study [40] from Bangladesh reported that 36% of children with uncomplicated SAM have elevated CRP and α1-glycoprotein. Assuming that 35% of children with uncomplicated SAM might have a subclinical infection [40], a randomization sequence will be generated using online software. The allocation will be concealed centrally in the institute. Based on the intervention plan, study participants and administrators will not be masked in the study.

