### Operational Definitions

Children with uncomplicated SAM are clinically well (ie, without signs of infection) and with a retained appetite (passed the appetite test), which is considered indicative of the absence of severe metabolic disturbance. SAM is defined as WHZ<–3 SD of the median WHO child growth standards and/or by the presence of bilateral pitting edema. Nonresponse to treatment is defined as children who do not meet discharge criteria (WHZ>–2 SD) after 4 months.

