### Data Entry and Analysis

#### Phase 1

Data will be entered into the Epicollect5 mobile app and analyzed in Stata version 18.0 software. Continuous variables (age, weight, height, WBC count, ESR, hs-CRP, procalcitonin, and colony-forming units) will be expressed as mean (SD) or median (IQR) based on data distribution. Categorical variables (clinical infection, subclinical infection, and AMR) will be expressed as percentages. The association between independent factors (sociodemographic, health, and nutritional factors) and of clinical/subclinical infection and AMR outcomes will be analyzed using chi-square tests, *t* tests, or Mann-Whitney *U* tests. Multivariate analysis using log-binomial regression will be performed to adjust for confounders. *P*<.05 will be considered statistically significant.

#### Phase 2

English transcripts will be prepared within 24 hours of conducting an IDI/FGD. Qualitative data will be analyzed in Atlas Ti software. First, complete transcripts will be read by the investigators to ensure immersion, initial codes will be generated inductively using inductive coding in Atlas.ti software, and the codes will be iteratively refined through discussions and organized into subcategories (subthemes) and higher-order categories (themes) in line with reflexive thematic analysis principles [42]. An audit trail (coding decisions, evolving codebooks, and notes from analytical discussions) will be maintained throughout the process to support confirmability and dependability. We will also perform data triangulation of qualitative and quantitative data to increase the credibility of the information collected about knowledge, barriers, and facilitators related to antibiotic usage among children with uncomplicated SAM by adopting convergent parallel mixed methods design.

#### Phase 3

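### The Phase 1 size of 606 does not follow from its stated inputs, and its 10% relative precision holds only at a 50% respiratory infection rate that does not fit the enrolled children or the Phase 1 objective

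*Protocol article*

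**What the plan says.** The protocol article, Sample Size, Phase 1, first cites a range of 15% to 68% for clinical infection. That range comes from children with complicated SAM. The plan then turns to uncomplicated SAM and gives its inputs: "Considering 50% prevalence of lower respiratory tract infection among children with uncomplicated SAM, 95% CIs, 10% relative precision, 1.5% design effect, 10% nonresponse rate", together with a 5% type I error. It concludes that "we will require 606 participants aged 6-59 months with uncomplicated SAM".

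Three other places bear on this:

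- Operational Definitions describes the population: "Children with uncomplicated SAM are clinically well (ie, without signs of infection) and with a retained appetite". The Background section likewise describes uncomplicated SAM as free of fever and clinical infection.
- Study Objectives sets the Phase 1 target as the prevalence of clinical or subclinical infection and the resistance patterns. Lower respiratory infection is not singled out.
- Study Procedure, Phase 3, uses another planning value when describing the randomisation: "Assuming that 35% of children with uncomplicated SAM might have a subclinical infection".

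**The concern.** The printed size should follow from the printed inputs, and the assumed prevalence should belong to the quantity being estimated in the children being enrolled. Neither holds as written. The Rationale section says infection rates must be assessed to judge whether empirical antibiotics are relevant, so Phase 1 prevalence is evidence that readers will rely on. If the stated 10% relative precision depends on a rate that does not apply to these children, the estimate will be less precise in relative terms than the plan promises.

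**Working it through.** **Inputs** (Sample Size, Phase 1): p = 0.50; 10% relative precision, so d = 0.10 × 0.50 = 0.05; z = 1.96; nonresponse 10%; design effect printed as 1.5% and read as 1.5.

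**Formula:** n = z² p(1 − p) / d², multiplied by the design effect, then inflated for nonresponse r either by dividing by (1 − r) or by multiplying by (1 + r).

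**Step 1. Try to reproduce 606.**

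- Base: 1.96² × 0.25 / 0.05² = 384.2.
- With design effect 1.5: 384.2 × 1.5 = 576.2.
- With 10% nonresponse: 576.2 / 0.9 = 640.3, rounded up to 641; or 576.2 × 1.1 = 633.9, rounded up to 634.
- With 5% nonresponse: 576.2 / 0.95 = 606.6; or 576.2 × 1.05 = 605.1, rounded up to 606.

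So 606 matches 5% nonresponse, not the printed 10%.

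**Step 2. Other readings.** Taking the design effect literally as 1.015 gives 434 or 429, so 1.5% is almost certainly a misprint for 1.5. With the other inputs kept, z = 1.645 gives 452 or 447, z = 2 gives 667 or 660, and absolute precision of 10 points gives 161 or 159. A finite population correction would come close to 606 only with roughly 5,000 to 10,000 eligible children. The plan states no such correction, and its figure of about 50 new cases a month (Study Area) implies 600 to 1,200 children over 12 to 24 months, which would give 391 to 486 (dividing by 0.9).

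**Step 3. Size needed at the plan's other value, p = 0.35.** Here d = 0.10 × 0.35 = 0.035.

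- Base: 1.96² × 0.35 × 0.65 / 0.035² = 713.4.
- With design effect 1.5: 1,070.1.
- With 10% nonresponse: 1,190 (dividing) or 1,178 (multiplying).

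That is about twice 606. A prevalence of 50% gives the largest n when precision is absolute. When precision is relative, n rises as prevalence falls.

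**Step 4. Precision that 606 delivers.** Half-width = 1.96 × √(1.5 × p(1 − p) / n).

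| Children analysed | p = 0.50 | p = 0.35 |
|---|---|---|
| 606 (all) | ±4.9 points, 9.8% relative | ±4.7 points, 13.3% relative |
| 576 (5% nonresponse) | ±5.0 points, 10.0% relative | ±4.8 points, 13.6% relative |
| 545 (10% nonresponse) | ±5.1 points, 10.3% relative | ±4.9 points, 14.0% relative |

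**Step 5. Absolute precision.** If ±5 points was meant, p = 0.35 needs 1.96² × 0.2275 / 0.05² = 349.6; × 1.5 = 524.4; with 10% nonresponse, 583 or 577. The planned 606 is enough.

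**The case against.** **The arithmetic slip is immaterial.** The Abstract and a Table 1 footnote can be read as saying that 606 children are actually sampled. At 50% prevalence that gives 9.8% relative precision, which meets the target, and even 545 gives 10.3%. This stands: the slip is worth correcting but does little harm by itself.

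**35% and 50% are different quantities.** The 35% rests on raised inflammatory markers and is used for the randomisation, whereas Phase 1 covers clinical and subclinical infection assessed by several markers and cultures. This also stands. The 35% is not proof of the true rate; it is the only other planning value in the document, and it is closer to what Phase 1 can mainly observe.

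**The 50% might be right.** A reader might infer from the definitions that 50% is impossible. The documents do not go that far: the Phase 1 inclusion criteria require no signs of complications and a passed appetite test, and the Outcomes section plans to measure clinical infection. The premise is in tension with the definition; it is not ruled out. Equally, the 50% acute respiratory infection figure quoted in the Introduction does not rescue it. That figure is not for lower respiratory infection, is not stated to concern uncomplicated SAM, and sits beside a survey figure of 2.8%.

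**Clustering.** A reader might infer that the Phase 1 analyses wrongly ignore the clustering allowed for in the size, since the plan says only that "Multivariate analysis using log-binomial regression will be performed to adjust for confounders". The documents do not support calling this an error. The analysis section does not specify how standard errors are computed, no cluster sampling is described (all eligible children are to be contacted), and such detail is commonly left to an analysis plan.

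**Conclusion.** The point holds in two parts. First, the stated inputs give 634 or 641, not 606; the printed figure corresponds to about 5% nonresponse, and the design effect is misprinted. The effect on precision is small. Second, and more important, the claimed 10% relative precision depends on a lower respiratory infection rate that is in tension with the enrolled population and is not the Phase 1 objective. At 35% subclinical infection, relative precision is 13.3% to 14.0%, depending on whether 606, 576 or 545 children are analysed.

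These figures assume a design effect of 1.5, and they treat 35% as a planning value for a related but different quantity. A reader might infer that the sample must be doubled. That does not follow: an absolute target of ±5 points is still met at 35%. What is wrong is the stated justification and precision, not necessarily the number of children.

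**What to change.** Keep 606 and rewrite the Phase 1 paragraph:

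1. Print the design effect as 1.5.
2. Either correct the nonresponse rate to 5% (about 576 analysable), or keep 10% and state that about 545 are analysable.
3. Replace the lower respiratory infection premise with the Phase 1 endpoint, subclinical infection, at the plan's own 35%.
4. State the precision that matches the choice in item 2: ±4.8 points (13.6% relative) for 576, or ±4.9 points (14.0% relative) for 545. If all 606 are to be analysed with no allowance for nonresponse, it is ±4.7 points (13.3% relative). Alternatively, state the target as an absolute ±5 points, which 606 meets at 35%.

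At most, add a sentence that the prevalence intervals will use the same clustering assumption as the size calculation.

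The cost is wording only. The relative precision on paper becomes less favourable, and no recruitment changes.

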### Outcomes

The primary outcomes of the RCT are as follows:

Weight gain at 16 weeks and 6 months after intervention initiationWHZ at 16 weeks and 6 monthsMUAC at 16 weeks and 6 monthsAnthropometric measurements collected by trained study staff using standardized procedures and calibrated equipment: weight measured using digital weighing scales; height/length using stadiometers or infantometers, as appropriate; and MUAC using standardized MUAC tapes

The secondary outcomes include the following:

Time to nutritional recoveryNutritional status at follow-up, categorized as cured (WHZ>−2 SD), nonresponder (WHZ<−2 SD), or lost to follow-upTransfer to inpatient careClinical signs of infection and morbidity episodes, including fever, diarrhea, and respiratory symptomsRecurrent infections during follow-upHemoglobin levelsAdverse events related to antibiotic therapyMortality

Clinical outcomes and morbidity episodes will be assessed during scheduled follow-up visits through caregiver interviews and clinical examination by trained study personnel. Hemoglobin levels will be estimated using standard laboratory methods. Information related to inpatient referrals, adverse events, and mortality will be documented using study follow-up records.

The exploratory outcomes include the following:

Proportion of children with clinical infections based on clinical evaluation resultsProportion of children with subclinical infections assessed using hs-CRP, procalcitonin levels, blood culture, and urine cultureGrowth in stool culturePatterns of antimicrobial sensitivity and resistance among children with uncomplicated SAMHealth-seeking behavior, antibiotic usage patterns, and care preferences among caregivers of children with uncomplicated SAMChallenges and facilitators in the management of uncomplicated SAM, as perceived by health care providers

Blood, urine, and stool samples will be collected and processed using standard microbiological and laboratory procedures to assess infection status and AMR patterns. Qualitative data will be collected through FGDs and IDIs using semistructured interview guides.

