Data analysis will be performed in Stata version 18.0 software using intention-to-treat analysis at the end of the study. Per protocol analysis will also be performed as a secondary analysis at the end of the study. Interim analysis will be part of the quality parameter (at the end of the first year). The WHZ and MUAC will be expressed as mean (SD) or median (IQR) with 95% CIs based on data normality. The presence of bilateral pitting edema will be expressed as proportions with 95% CIs. Independent variables (child’s age in months and mother’s age) will be expressed as mean (SD) or median (IQR) with 95% CIs based on data normality. Factors such as education status, type of delivery, and birth complications will be expressed as proportions with 95% CIs. Outcomes such as episodes of acute illness, day care absenteeism, parenteral absenteeism, number of hospital visits, and food consumption will be expressed as mean (SD) or median (IQR) with 95% CIs based on data normality. Outcomes such as the presence of sepsis and mortality status will be expressed as proportions with 95% CIs. The chi-square test will be performed to analyze the association between outcomes and categorical independent variables. An unpaired *t* test (or Mann-Whitney *U* test) will be performed to assess the association between outcomes and continuous independent variables. Poisson regression analysis (bivariate and multivariate) will be conducted to explore the association between dependent and independent factors. Adjusted risk ratios with 95% CIs will be reported for factors included in the multivariate Poisson regression model.

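### The sample-size calculation covers one two-arm test of WHZ at 2 weeks, but the RCT declares six unranked primary outcomes in three arms, none of them at 2 weeks

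*Protocol article*

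**What the plan says.** The Phase 3 part of Sample Size relies on one earlier Indian trial, which "reported the WHZ mean (SD) as –1.29 (0.84) in the amoxicillin group and –1.45 (0.93) in the control group", measured "at the end of 2 weeks of intervention". From these it concludes: "Considering these values, with 95% CI and 80% power, we will require 480 participants in each group". It then sets the number aside. "Considering logistic issues, feasibility, and long follow-up", it says, "we will recruit 250 children aged 6-59 months with uncomplicated SAM per group".

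The Outcomes section opens its list with "The primary outcomes of the RCT are as follows" and names weight gain, WHZ and MUAC, each at 16 weeks and at 6 months. (The last item of that list describes how measurements are taken and is not a further outcome.) No outcome or time point is placed first.

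The third primary objective compares amoxicillin, azithromycin and no antibiotic without naming a lead contrast. Allocation differs by stratum (Study Procedure, Phase 3). Children with subclinical infection go only to one of the two antibiotics. For the others, "Children without any subclinical infection will be randomized to the amoxicillin, azithromycin, or control group in a 1:1:2 randomization sequence". Children recruited after phase 1 are allocated 1:1:1.

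**The concern.** Two things that this article itself fixes do not fit together: what counts as primary, and what the sample-size calculation was for. The calculation allows for one contrast, one measure and one time. The trial has up to three contrasts, three measures and two times, and the sizing time is not among them. So the stated 80% power belongs to no declared primary outcome unless the 2-week difference and SDs are assumed to hold at 16 weeks or 6 months.

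The Discussion says the results could support revisiting guidelines on empirical antibiotics. With six primaries of equal rank, a chance benefit on one measure at one time, or a mixture of positive and null results, could be read either way.

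**Working it through.** **Inputs from the documents.** WHZ means -1.29 and -1.45 (difference 0.16); SDs 0.84 and 0.93; 95% confidence, read as two-sided alpha 0.05; power 80%; 480 calculated and 250 planned per group; six primary outcomes; three arms.

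**1. Reproducing 480.** n = (1.960 + 0.842)² × (0.84² + 0.93²) / 0.16² = 481.5 per group, in line with the stated 480. A one-sided test would give 380. So 480 is one two-sided 5% test, with no allowance for a third arm or for other outcomes.

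**2. Number of comparisons.** 3 measures × 2 times = 6 outcomes. Three arms give 3 pairwise contrasts, and 6 × 3 = 18. With only the two antibiotic-control contrasts it is 6 × 2 = 12.

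**3. False-positive risk if each comparison is tested at 5% and any one counts.** Simulation with no true effect, three equal arms and six correlated normal outcomes. The documents give no correlations, so a range is assumed:

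| Correlation between measures / between times | All three contrasts (18 tests) | Two antibiotic-control contrasts (12 tests) |
|---|---|---|
| 0.9 / 0.9 | 26% | 20% |
| 0.8 / 0.8 | 33% | 26% |
| 0.5 / 0.6 | 45% | 36% |
| 0.3 / 0.3 | 51% | 41% |

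**4. Power if alpha is split.** Pooled SD = √((0.84² + 0.93²)/2) = 0.886. SE = 0.886 × √(2/n), which is 0.0572 at 480 and 0.0793 at 250. Power = Φ(0.16/SE - z), where 0.16/SE is 2.797 and 2.019 respectively:

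| Alpha | z | Power at 480 | Power at 250 |
|---|---|---|---|
| 0.05 | 1.960 | 79.9% | 52.3% |
| 0.05/3 | 2.394 | 65.7% | 35.4% |
| 0.05/18 | 2.991 | 42.3% | 16.5% |

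These apply the 2-week difference and SDs to whichever outcome is tested, for want of other inputs.

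**5. What the allocation scheme does to a test across arms.** Take the plan's own 35% subclinical infection, all 606 phase 1 children entering the RCT, and 150 later recruits with the same infection rate.
- Infected in phase 1: 0.35 × 606 = 212, or 106 to each antibiotic.
- Uninfected: 394, allocated 98.5, 98.5 and 197.
- Later recruits: 50 per arm, of whom 0.35 × 50 = 17.5 infected.
- Infected share in each antibiotic arm: (106 + 17.5)/(106 + 98.5 + 50) = 123.5/254.5, about 49%.
- Infected share in control: 17.5/(197 + 50), about 7%.

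If infection status affects growth, an unstratified comparison with control can reject for that reason alone.

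**6. Power for amoxicillin versus control within strata that include control.** The information is 1/(1/98.5 + 1/197) + 1/(1/50 + 1/50) = 65.7 + 25 = 90.7. SE = 0.886/√90.7 = 0.0931, 0.16/0.0931 = 1.719, and power = Φ(1.719 - 1.960), about 40% at 5%. With 200 later recruits the second term is 33.3, the total 99.0 and the power about 43-44%.

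**The case against.** The strongest reply is that the article never says 18 pairwise tests will be run at 5% with any one taken as success. The P<.05 threshold appears only under the Phase 1 analysis. The Phase 3 text speaks of two-group tests in general terms ("An unpaired *t* test (or Mann-Whitney *U* test) will be performed to assess the association between outcomes and continuous independent variables") and then of Poisson regression. A multiplicity procedure may sit in an analysis plan that is not shown. All of this stands. A reader might infer that the trial as planned carries a false-positive risk of one in three or more. The documents do not support that, because the figure depends on a decision rule they do not state and on correlations they do not give. Nor is the absence of a multiplicity rule here a fault in itself.

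A reader might also infer that multiplicity is what costs the trial its 80% power. It is not the first cause. The article attaches 80% to 480 and does not claim it for 250; the cut to 250 on feasibility grounds brings power on the plan's inputs to about 52% before any error control.

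What the reply does not remove is the mismatch. An unseen multiplicity rule that splits alpha would make 80% at 480 untrue, and leaving alpha unsplit would make the overall 5% untrue. In neither case does the calculation describe the primary outcomes listed. The choice of lead outcome does belong to the investigators: the objective names weight gain first, so WHZ is not the only defensible choice.

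**Conclusion.** The point holds as a mismatch between a single-test calculation and six unranked primary outcomes in three arms, with a sizing time point that is none of them. The reproduction of 480, the count of up to 18 comparisons and the power figures follow from the article's own inputs, provided the 2-week difference and SDs carry over to the later times. The false-positive range of 26-51% (20-41% for antibiotic-control contrasts only) is conditional on the assumed correlations, equal arms, 5% per test and any-one-success. Even its lower end is several times 5%, so the direction does not depend on the exact correlation. It should be corrected before the RCT starts. The article reports that this component is delayed, so the change can still precede outcome data.

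**What to change.** 1. In Outcomes, name one primary outcome at one time point. WHZ at 16 weeks is the natural candidate because WHZ is the measure used for sizing, but the investigators may choose another. Make the rest secondary or put them in a fixed testing order.
2. For that outcome, test equality of the three arms at 5%, and test the pairwise contrasts at 5% each only if the overall test is significant. With exactly three groups this holds the family-wise error at 5% without splitting alpha.
3. Stratify every one of these tests by the randomisation strata, and draw comparisons with control only from strata in which control was an allocation option. Without this, the imbalance in step 5 of the working means the 5% level cannot be relied on.
4. In Sample Size, restate power for that outcome, time point and procedure at 250 per group, giving the assumed difference and SD.

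The cost is wording in the protocol and registry plus one overall test, with no extra children or visits. The other outcomes lose primary status, and no pairwise claim can be made when the overall test is not significant. The restated power will be low: about 40-44% for amoxicillin versus control on the present inputs (step 6), and somewhat less once the overall test must also be passed.
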